### **3.3 Discontinuation of Study Treatment/Withdrawal from the Study**

All subjects may discontinue the study treatment or withdraw from study at any time. If a subject terminates study treatment or withdraws from the study, the investigator should record the causes for study treatment discontinuation or study withdrawal in the eCRF, and complete the visit specified by the protocol.

#### **3.3.1 Termination of study treatment**

The causes for subjects' discontinuation of study treatment may include:

- AE;
- Lost to follow-up;
- Death;
- Subjects with poor compliance are not suitable for continuing the study, as judged by the

[figure not shown]

investigator.

- The subject withdraws the ICF;
- New anticancer treatment is started;
- Termination of the study by the sponsor;
- PD;
- Others (e.g., the subject can no longer benefit from the study treatment when continuing the study at the discretion of investigator).

For subjects terminating study treatment, see Sections 7.6 and 7.7 for treatment termination and follow-up procedures. For subjects who terminate study treatment due to AEs, investigators will follow up them until the AEs are resolved or stable.

### **3.3.2 Withdrawal from the Study**

All follow-up procedures will be stopped if a subject withdraws from the study. Reasons for withdrawal from the study may include:

- Death;
- Lost to follow-up;
- The subject withdraws the ICF for participation in the study (including follow-up period);
- The sponsor terminates the study.

### **3.4 Patient Re-screening Policy**

For subjects who do not meet the protocol requirements during their initial screening, once their informed consent is obtained, re-screening is allowed (only 1 re-screening can be performed). When subjects are re-screened at the same site, the subject screening number must be the same as the original. Reasons for subjects not being enrolled after initial screening will be recorded in the medical record. For re-screened subjects at the same site, the data from the initial screening will not be recorded in the EDC.

### **3.5 Site Closure**

The sponsor, Ethics Committee, drug clinical trial institution and investigator can suspend or terminate the clinical trial according to the risk/benefit assessment of clinical trial, inform mutually and describe the reasons.

If the sponsor suspends or terminates the study prematurely, the sponsor will promptly inform all participating investigators, drug clinical trial institutions, Ethics Committees and provincial drug regulatory authorities, National Medical Products Administration, and clarify the reasons.

[figure not shown]

## 4 Clinical Study Plan

### 4.1 Study Design

This is an open-label, multicenter, Phase I clinical trial which is designed to determine the safety and tolerability of HQP1351 in patients with advanced GIST and other solid tumors, to determine RP2D, and to assess the preliminary efficacy of HQP1351 in patients with advanced GIST and other solid tumors. Patients with histologically and/or cytologically proved, advanced and/or metastatic GIST or other solid tumors will be enrolled. Among them, GIST patients must have primary resistance to imatinib or have failed treatment with imatinib plus at least one other TKI. In some rare cases, GIST patients who have failed imatinib treatment alone may also be included in this study if considered to be eligible for enrollment after careful judgment by the investigator.

As of February 2021, HQP1351 has undergone a total of 9 clinical studies, and preliminary results from the Phase I and Phase II clinical trials that have been conducted show a favorable safety profile in the dose range of 50 mg QOD. HQP1351 (olverembatinib tablets) has been granted conditional marketing authorization from the National Medical Products Administration on November 24, 2021 (approval number: NMPA H20210048). It is indicated for the treatment of "adult patients with tyrosine kinase inhibitor (TKI)-resistant chronic phase chronic myeloid leukemia (CML-CP) or accelerated-phase CML (CML-AP) harboring the T315I mutation as confirmed by a validated diagnostic test", and the recommended dose is 40 mg QOD.

The study is initially designed as a Phase I study with standard 3+3 dose escalation. Based on the study results of HQP1351 SJ-0002 in CML patients and the consensus reached at the SJ-0003 kick-off meeting with the investigator, this study will explore the safety in the 30 mg, 40 mg, and 50 mg dose groups in parallel, and 10 subjects will be enrolled by means of randomization at each dose level using the IWRS. After preliminary adult data are available, adolescent subjects with advanced and/or metastatic wild-type GIST will be included. The dosage for adolescents is based on the adult dose and the selected dose will be adjusted according to their body weight. If the subject's body weight is  $\geq 40$  kg, the dose of 40 mg QOD will be given based on the adult dose. If the subject's body weight is  $\geq 30$  kg and  $< 40$  kg, the dose of 30 mg QOD will be given. If the subject's body weight is  $\geq 20$  kg and  $< 30$  kg, 20 mg QOD will be given. Based on the safety data from 9 clinical studies that have been conducted with HQP1351 and the safety and efficacy data of 36 patients already enrolled in this study, 40 mg QOD is selected as the dosage for non-randomized adult subjects after discussion between the investigator and the sponsor.

HQP1351 tablets will be administered orally to eligible subjects once every 2 days in a 28-day cycle. Subjects will receive treatment until PD, intolerable toxicity, death, or termination of treatment for any other reason. If a subject is assessed to have PD according to the RECIST v1.1 criteria, but the investigator determines that the subject will benefit from continuing the

[figure not shown]

study, then the subject may continue to take HQP1351 and undergo safety follow-up yet no more efficacy follow-up after PD is documented. During medication, subjects will not receive other antitumor study drugs, marketed drugs, or treatment methods other than HQP1351. Symptomatic (including those directed at controlling symptoms resulting from the patient's malignancy) and supportive treatments are allowed.

In the standard 3+3 dose escalation part of this study, blood samples from subjects in Cycle 1 will be collected for the PK analysis of HQP1351. In the randomized part, 1-3 study sites will be selected to collect the blood samples of the first 3 enrolled subjects in each dose group in Cycle 1 for the PK analysis of HQP1351. If for any reason complete PK samples are not obtained from the first 3 subjects, they will be replaced by subjects subsequently enrolled in the dose group until complete PK samples are obtained from 3 subjects. PK blood samples will be collected from all non-randomized adult subjects receiving a fixed dose of 40 mg QOD for PK analysis. PK blood samples will be collected from all adolescent subjects for PK analysis.

Biological samples will be collected from all subjects for relevant biomarker testing and assessment.

All subjects will undergo efficacy assessment every 8 weeks during treatment, along with assessment of safety information such as AEs and laboratory tests.

Subjects enrolled in the Phase I study with standard 3+3 dose escalation who have received at least one cycle of HQP1351 after this protocol amendment takes effect, and have not experienced related or possibly related Grade  $\geq 2$  toxicity nor have tumor progression, may receive a higher dose of HQP1351 upon their own informed consent after discussion between the investigator and the sponsor. The subject will continue to be followed up according to the protocol, but will not be included in the number of randomized subjects.

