### **1.6 Risk-benefit and Ethical Assessment**

Available clinical data suggest that HQP1351 is well tolerated in patients with GIST at dose levels of 30 mg, 40 mg, and 50 mg and is effective for the treatment of advanced GIST, with a positive benefit/risk ratio.

As of August 2021, 6 wild-type GIST subjects were enrolled, all of whom had previously been treated with  $\geq 1$  targeted drug (3 had previously been treated with 3 drugs, 2 with 2 drugs, and 1 with a targeted drug). The preliminary efficacy assessment was PR in 1 subject (archived in Cycle 9, which remained PR when followed up to Cycle 13), SD in 3 subjects (followed up for more than 11 cycles, up to 31 cycles), SD in 1 subject when followed up to Cycle 3, and PD in 1 subject on Day 52 of medication, proving certain efficacy for wild-type GIST. Pediatric children with metastatic GIST are very rare, and more than 85% of them are wild-type with primary resistance to imatinib and no standard treatment available, facing the predicament of no medicine available for treatment. Given that the National Medical Products Administration encourages the inclusion of adolescents in tumor clinical trials as much as possible, after the preliminary adult data (currently there are safety data and preliminary PK data and efficacy data from more than 300 subjects) are available, it is planned to include adolescent wild-type GIST subjects over 12 years old without standard treatment in clinical trials for adult so as to enable these adolescent GIST patients to have the opportunity to enter clinical trials, obtain their clinical data as soon as possible, and solve the problem of no medicine available for these extremely rare patients.

More information about the known and expected benefits and risks of HQP1351 can be found in the relevant section of the Investigator's Brochure (IB) for HQP1351. The sponsor, CRA, and investigators will conduct the study in accordance with the study protocol, the Good

[figure not shown]

Clinical Practice (GCP), the International Council for Harmonization of Technical Requirements for Pharmaceuticals for Human Use (ICH) guidelines, and applicable regulatory requirements.

[figure not shown]

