### 3 Trial Population

#### 3.1 Inclusion Criteria

Subjects will be eligible for the study if they meet each of the following criteria:

1. Aged  $\geq 12$  years, male or female.
2. Advanced and/or metastatic GIST or other solid tumors, confirmed by histology and/or cytology. Among them, GIST patients must have primary resistance to imatinib (tumor progression within 6 months after first-line use of imatinib, or immunohistochemical presence of SDHB expression deletion or NF1 mutation) or have failed treatment with imatinib or imatinib plus at least one other TKI (following initial imatinib or other TKI treatment for more than 6 months, the subject has tumor progression again after achieving a response or stable disease).
3. ECOG score  $\leq 2$ .
4. Life expectancy of  $\geq 3$  months.
5. Hematologic function as outlined below:
  - Absolute neutrophil count (ANC)  $\geq 1.5 \times 10^9/L$  (ANC achieved by colony-stimulating factors will not be used);
  - Platelet count  $\geq 100 \times 10^9/L$  (baseline platelet count achieved by blood transfusion or thrombopoietic growth factor will not be used);
  - Hemoglobin  $\geq 90$  g/L  
Note: If hemoglobin is stable for 14 days after transfusion (a decrease of no more than 10 g/L), transfusion is allowed. The use of erythropoiesis-stimulating agents (ESAs) is allowed;
  - Serum albumin  $\geq 30.0$  g/L;
  - Serum lipase  $\leq 1.5 \times$  upper limit of normal (ULN);
  - Serum amylase  $\leq 1.5 \times$  ULN.
6. Hepatic and renal function:
  - Serum creatinine  $\leq 1.5 \times$  ULN; or serum creatinine  $> 1.5 \times$  ULN, and creatinine clearance  $\geq 50$  mL/min;
  - Serum total bilirubin  $\leq 1.5 \times$  ULN;
  - Aspartate aminotransferase (AST) and alanine aminotransferase (ALT)  $\leq 2.5 \times$  ULN ( $\leq 5 \times$  ULN in the presence of liver metastasis).
7. Cardiac function parameters:
  - Troponin (I or T)  $\leq$  ULN;

[figure not shown]

- Ejection fraction (EF)  $> 40\%$ ;
  - QTc interval on electrocardiogram (corrected by Bazett's formula): male  $\leq 450$  ms and female  $\leq 470$  ms.
8. Women of childbearing potential should have a negative serum pregnancy test within 7 days prior to the first dose of the study drug.

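### The inclusion criteria admit adolescents with any advanced solid tumor, while the design and benefit-risk text cover only adolescents with wild-type GIST; the prior-TKI rule also differs between 3.1 and 4.1

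*Protocol*

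**What the plan says.** **Adolescents.** Inclusion criterion 1 in 3.1 reads "Aged $\geq 12$ years, male or female". Criterion 2 opens with "Advanced and/or metastatic GIST or other solid tumors, confirmed by histology and/or cytology" and then adds resistance requirements for GIST only. The synopsis criteria have the same content. The design text in the synopsis and in 4.1 says that, after preliminary adult data, "adolescent subjects with advanced and/or metastatic wild-type GIST will be included". Section 1.6 is narrower still: "it is planned to include adolescent wild-type GIST subjects over 12 years old without standard treatment in clinical trials for adult".

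**Prior TKI therapy in GIST.** Under criterion 2, GIST patients without primary resistance must "have failed treatment with imatinib or imatinib plus at least one other TKI". A parenthesis defines failure: more than six months on imatinib or another TKI, after which "the subject has tumor progression again after achieving a response or stable disease". Section 4.1 instead requires primary resistance or failure of imatinib plus at least one other TKI, and then adds: "In some rare cases, GIST patients who have failed imatinib treatment alone may also be included in this study", subject to careful judgment by the investigator.

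**Which text decides entry.** Section 7.2.2 has consented subjects assessed against 3.1 and 3.2. Section 7.2.1 bases eligibility in the randomized part on the investigator's review of the inclusion and exclusion criteria. Neither sends the site to 4.1 or 1.6.

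**The concern.** A site that follows the criteria as written can enroll a minor for whom the protocol makes no case. The argument in 1.6 for opening the trial to adolescents rests on early results in six wild-type GIST subjects, and on metastatic GIST in children being mostly wild-type, with primary imatinib resistance and no standard treatment. None of that carries over to an adolescent with another solid tumor or with KIT-mutant GIST.

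The prior-therapy wording has a milder version of the same fault. One patient is a routine entrant under 3.1 and an exception under 4.1, so sites may apply the rule differently. It is then also unclear whether admitting such a patient, or an adolescent outside the 4.1 description, is a protocol violation. That matters because major violations remove a subject from the per-protocol set (10.3).

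**Working it through.** No calculation applies, because the point depends on no sample size, rate or event count. The check sets the texts side by side and runs test patients through them.

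| Rule | 3.1 and synopsis criteria | 4.1 and synopsis design text | 1.6 |
|---|---|---|---|
| Adolescent tumor type | GIST or any other solid tumor | wild-type GIST | wild-type GIST |
| No standard treatment | no condition | no condition | stated |
| Adult data first | no condition | stated | stated, and said to be available |
| Lower age limit | 12 or older | none given | over 12 |
| Imatinib-alone failure | ordinary route, with failure defined | rare cases, by judgment (4.1 only) | not addressed |

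**Does any exclusion criterion close the adolescent gap?** None of the 20 items in 3.2 mentions age, wild-type status or availability of standard treatment. Item 20 lets the investigator or sponsor refuse a subject on grounds of safety or interference with the safety assessment. That is a general discretion and does not define a population.

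**Do the screening procedures close it?** Section 7.2.2 lists SDHB immunohistochemistry. KIT and PDGFRa testing belongs to the exploratory biomarker work in 7.9, where the sampling table marks tumor tissue as optional. No step requires wild-type status to be established before an adolescent enters.

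**Test patients, each assumed to meet all other criteria:**

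1. Age 13, advanced non-GIST solid tumor. Criteria 1 and 2 are met and no population exclusion applies. The patient is outside the adolescent group in 4.1 and 1.6.
2. Age 13, KIT-mutant GIST with qualifying imatinib resistance. The result is the same.
3. Exactly 12 years old, wild-type GIST with qualifying resistance. Admitted by 3.1; doubtful under the age wording in 1.6.
4. Adult GIST, more than six months of imatinib, stable disease and then progression, no other TKI. Routinely eligible under 3.1; a judged exception under 4.1.

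Patients 1 and 2 show the main contradiction. Patient 3 is a wording slip. Patient 4 shows the minor contradiction: both sections can admit the patient, but on different terms.

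The missing adult-data condition matters little now, since 1.6 reports safety data and preliminary PK and efficacy data from more than 300 subjects.

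**The case against.** **What can be said for the text.** Section 4.1 says that adolescents with wild-type GIST will be included; it does not say that others will not. Section 15.3 requires staff to read and follow the whole protocol, so 4.1 is an instruction too. On prior therapy, both 3.1 and 4.1 admit imatinib-alone failure, and the qualifier in 4.1 has no cap or objective test. Nobody eligible under 3.1 is categorically barred by 4.1.

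**What of this stands.** The last argument stands and makes the prior-therapy mismatch minor. The first two do not rescue the adolescent text. Read with 1.6, which argues for one group only, the restrictive meaning of 4.1 is the natural one. If 4.1 binds sites as much as 3.1 does, they hold two conflicting instructions, and that is the fault.

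**Stronger readings that the documents do not support:**

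- That 1.6 also limits imatinib-alone failure. It does not mention it; that limit is in 4.1 only.
- That any imatinib-alone failure qualifies. Criterion 2 requires the treatment duration and the prior response or stable disease given above.
- That the mismatch is what mixes treatment lines in ORR and PFS. The 4.1 population is already mixed: it admits primary resistance, which under criterion 2 includes progression within six months of first-line imatinib. Aligning the wording would not remove the mix.
- That each off-target subject is a known share of the efficacy result. One subject in the 10 to 20 of the non-randomized part is 1/20 to 1/10, or 5% to 10%, but 10.1 does not say whether adolescents count in that number, and 10.4.2 analyses efficacy on the full analysis set.
- That the lack of a weight criterion is a comparable gap. The dosing bands start at 20 kg, and nothing in the documents suggests that a lighter subject aged 12 or over is a realistic case.

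**Conclusion.** The concern holds as an internal inconsistency. The main part is that criteria 1 and 2 admit adolescents whom neither the design text nor the benefit-risk text covers, and no exclusion criterion or screening step prevents it. The minor part is that 3.1 treats defined imatinib-alone failure as routine and 4.1 as rare.

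The conflict should be corrected because it concerns minors and the correction is cheap. It does not undermine the primary safety assessment. Its practical effect cannot be quantified: the protocol gives no planned number of adolescents and does not show that anyone outside the described population was enrolled. Section 1.5 describes the 36 GIST subjects enrolled by January 31, 2021 as TKI-resistant and heavily pretreated.

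The conclusion rests on two readings: that sites decide entry on 3.1 and 3.2, as 7.2.2 directs, and that the adolescent sentence in 4.1 is meant restrictively, as 1.6 implies. It takes no view on which population or prior-therapy rule is clinically right.

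**What to change.** Reconcile 3.1, the synopsis criteria and design text, 4.1 and 1.6 so that all state one adolescent population, including the lower age limit and whether lack of standard treatment is required, and one prior-TKI rule for GIST.

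The sponsor can do this in either direction:

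- carry the restrictions in 4.1 and 1.6 into criteria 1 and 2; or
- if the broader population is intended, revise 4.1 to say so and extend the benefit-risk justification in 1.6 to the adolescents it does not now cover.

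The cost is a short amendment with the usual ethics committee approval. The first option may exclude a few subjects who are admissible now; the second requires a benefit-risk argument that the protocol does not yet contain.

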## 4.2 Intolerable Toxicity

Intolerable toxicity is defined as:

- An AE that may affect the subject's ability to continue study-specific procedures or is not in the subject's best interest, at the discretion of the investigator or the Sponsor.
- Toxicity requiring more than twice dose reductions of HQP1351.
- HQP1351 allergy and serious allergic reactions (e.g., hypotension, bronchospasm, and/or rash generalised/erythema).

Subjects who experience intolerable toxicity will permanently discontinue the study unless it is in the subject's best interest to continue the study after the investigator has evaluated the subject's risks and benefits and discussed with the Sponsor.

[figure not shown]

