#### **4.3.2 Dose adjustment**

AEs that occur during this study will be graded according to National Cancer Institute-Common Terminology Criteria for Adverse Events (NCI-CTCAE) (v4.03). According to the correlation of AEs with the study drug and grade, the investigator will take different actions with the study drug, including maintaining the original treatment regimen, withholding dosing, reducing the dose, and terminating the treatment. Up to twice dose reductions are allowed, each to the next lower dose already explored. Any adult subject requiring a reduction of HQP1351 dose below 30 mg QOD should permanently discontinue the study treatment. The study drug can be resumed when the study drug-related toxicities resolve to grade 1 or below.

Dose adjustment may not be performed for grade 1/2 toxicities related to the study drug that can be treated by supportive treatment or don't influence normal daily activities of subjects, unless QTc prolongation, clinically significant pancreatitis, or other clinical conditions that affect subject's safety at the investigator's discretion. For intolerable (symptomatic or influencing subject's normal daily activities) or persistent (unable to be handled with the best supportive care and recovered to grade 1 or baseline after up to 2-week of drug withdrawal) grade 1/2 toxicities related to the investigational product, whether to make dose adjustment will be determined by discussion between the PI and the sponsor.

If a subject experiences grade 3 or 4 investigational drug-related toxicities, the investigational drug should be interrupted immediately. A maximum of 2 weeks (14 days) of drug interruption is permitted to resolve toxicities to Grade 1 or below, or baseline level. The investigational drug can be resumed when the toxicities resolve to Grade 1 or below, or baseline level. Each subject may undergo a maximum of twice dose reductions throughout the study period, and dose increases are generally no longer allowed after dose reductions. Please refer to Table 2-4 for guidance on dose adjustment for study drug-related toxicity.

[figure not shown]**Table 2: Dose delay and adjustment due to hematologic toxicities**

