**Table 4: Dose delay and adjustment due to general toxicities**

| Toxicity / NCI-CTCAE grade                                                   | Actions to be taken                                                                                                                                                                                                                               |
|------------------------------------------------------------------------------|---------------------------------------------------------------------------------------------------------------------------------------------------------------------------------------------------------------------------------------------------|
| Administration related reaction                                       | Please refer to 4.3.4.                                                                                                                                                                                                                            |
| Other Toxicities                                                      |                                                                                                                                                                                                                                                   |
| Grade 1                                                                      | 1. Monitor as clinically required.
2. No dose adjustment is required.                                                                                                                                                                          |
| Grade 2 or 3, clinically significant but uncontrollable with supportive care | 1. Interrupt HQP1351 administration for up to 2 weeks (14 days) until toxicity resolves to Grade $\leq 1$ .
2. Resume HQP1351 administration at a reduced dose level and monitor as needed.
3. A maximum of two dose reductions is allowed. |

[figure not shown]

| Toxicity / NCI-CTCAE grade | Actions to be taken                                                                                                                 |
|----------------------------|-------------------------------------------------------------------------------------------------------------------------------------|

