#### 4.3.3 Principles for management of serum troponin increased

If a subject develops serum troponin increased during treatment with HQP1351, the following measures are recommended:

- To evaluate cardiac function of the subject and recommend to perform the following examinations:
  - Serial serum troponin test
  - Echocardiogram
- TEE or PET scan to exclude direct heart injury due to tumor (when appropriate).
- Consult the Sponsor to determine whether subjects who continue the study will benefit the most.

Any AEs or SAEs caused by serum troponin increased should be reported as described in 9.2. For subjects with persistent heart injury during treatment with HQP1351, the Sponsor does not recommend special treatments based on the mechanism of action of HQP1351, but recommends routine supportive care and will handle with reference to the advice of internal medicine specialists and cardiologists.

#### 4.3.4 Treatments for patients who develop allergic reactions on or after Day 1

Potential allergic reactions or other inflammatory symptoms may be observed in subjects after HQP1351 is orally administered. Signs and symptoms of inflammation or allergy include: Fever, chills, chilliness, allergic reaction, rash, urticaria, measles, dizziness, hypotension, edema, bronchospasm, tachypnoea, flu-like symptoms, and other reactions.

Patients with symptoms and signs of allergy or similar reactions should be treated according to principles of the institution.

Prophylaxis should be given before each subsequent dose of treatment cycles to patients with allergy or similar reactions, including:

- 500 to 1,000 mg acetaminophen administered orally 30 minutes before dosing;
- 12.5 to 25 mg promethazine administered orally or intravenously 30 minutes before dosing;
- H1-receptor antagonists (e.g., loratadine) 30 minutes before dosing;

[figure not shown]

- Consider corticosteroids administered orally or intravenously according to the principles of the institution.
- The investigator will decide whether prophylactic administration of H1-receptor antagonists and/or corticosteroids is required. The investigator and the Sponsor will decide whether long-term prophylactic treatment is required in the cycles after allergic reactions are observed.

[figure not shown]

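### The allergic-reaction guidance that Table 4 points to (4.3.4) calls for premedicated re-dosing without limiting itself to reactions outside the 4.2 stopping rule

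*Protocol*

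**What the plan says.** Protocol 4.2 lists three kinds of intolerable toxicity. The third is "HQP1351 allergy and serious allergic reactions (e.g., hypotension, bronchospasm, and/or rash generalised/erythema". The consequence follows: "Subjects who experience intolerable toxicity will permanently discontinue the study unless it is in the subject's best interest to continue the study", and that exception depends on the investigator weighing risks and benefits and discussing the case with the Sponsor.

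Management of toxicity is in 4.3. Section 4.3.2 ends with "Please refer to Table 2-4 for guidance on dose adjustment for study drug-related toxicity". In Table 4, the whole instruction for an administration related reaction is "Please refer to 4.3.4".

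Section 4.3.4 opens with a list of what it covers: "Signs and symptoms of inflammation or allergy include: Fever, chills, chilliness, allergic reaction, rash, urticaria, measles, dizziness, hypotension, edema, bronchospasm", followed by tachypnoea, flu-like symptoms and an open category of other reactions. After leaving acute treatment to institutional practice, it says: "Prophylaxis should be given before each subsequent dose of treatment cycles to patients with allergy or similar reactions". It leaves the need for H1 antagonists and corticosteroids to the investigator. It gives the investigator and the Sponsor one joint decision, on long-term prophylaxis in later cycles.

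**The concern.** The same clinical event meets two different defaults. Under 4.2 a subject with bronchospasm or hypotension from an allergic reaction stops, unless a defined review supports going on. Under 4.3.4 the subject is premedicated and dosed again. A site that looks up the event where 4.3.2 and Table 4 direct it arrives at 4.3.4, which does not mention 4.2.

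At stake is a rechallenge after a potentially serious reaction without the review that the protocol itself requires. Safety and tolerability are the primary objective, and subjects are eligible from age 12. Sites could also differ in whom they discontinue for the same reaction, and so in what enters the listing of adverse events leading to discontinuation (10.4.3). No sample size or error rate is affected.

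**Working it through.** No formula applies; the check is a comparison of the sections.

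1. **Overlap of the reactions.** 4.2 gives three examples. 4.3.4 names 13 signs or symptoms.
   - Hypotension: in both.
   - Bronchospasm: in both.
   - Generalised rash or erythema: 4.3.4 has rash, with no extent given.

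   So two of three match by name and one in part. In addition, 4.2 lists allergy to HQP1351 with no severity attached, and 4.3.4 gives prophylaxis to patients with allergy. A mild-versus-serious split therefore does not separate the two sections on their wording.

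2. **Route from event to instruction.** 4.3.2 leads to Tables 2-4, the Table 4 row leads to 4.3.4, and 4.3.4 leads to premedication. Mentions of 4.2 in 4.3.1 to 4.3.4 and Tables 2-4: zero. Table 4's Grade 4 stop is placed under other toxicities, a different row from administration related reactions.

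3. **What 4.3.4 asks about continuing.** Nothing directly. Its joint decision concerns long-term prophylaxis. The neighbouring troponin section, 4.3.3, does put the question: "Consult the Sponsor to determine whether subjects who continue the study will benefit the most".

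4. **What 4.3.2 adds, by grade of related reaction.**
   - Grade 3 or 4: immediate interruption for up to 14 days. Resumption is allowed once the toxicity is back to Grade 1 or below, or to baseline. An acute reaction may well recover to that level, and the 4.2 review is not a condition of resuming.
   - Grade 1 or 2: no automatic interruption. The clause that begins "For intolerable (symptomatic or influencing subject's normal daily activities) or persistent" leads only to a discussion between the principal investigator and the sponsor on dose adjustment. It uses the word intolerable in its own local sense and does not alter 4.2.

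5. **Timing.** Dosing is every other day, 2 × 24 = 48 hours. Where nothing interrupts dosing, the next dose may be due within two days. Because of step 4, this applies to the lower grades only.

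6. **Result.** At grade 3 or 4 the gap opens at resumption; at lower grades it opens at the next scheduled dose. In both cases a site can follow the 4.3 instructions and re-dose without meeting the 4.2 condition.

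**The case against.** The strongest reply is that the sections do different jobs. 4.2 decides whether a subject may continue; 4.3.4 says how to treat and premedicate one who does. On that reading 4.3.4 serves subjects kept on under the 4.2 exception, and those with milder or non-allergic symptoms such as fever and chills. 4.2 needs no citation to bind: 4.1 makes intolerable toxicity an end of treatment, 4.2 immediately precedes 4.3, and 15.3 requires the whole protocol to be read and followed.

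There are further safeguards. 4.3.1 calls for an investigator-sponsor discussion about discontinuing for unexpected toxicity, which might apply. Serious events reach the sponsor within 24 hours, and 9.1.2 names rescue-treated allergic bronchospasm as an example. A joint decision on long-term prophylaxis also makes the question of continuing hard to avoid.

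Most of this stands. A reader might infer that the protocol contradicts itself, or that it instructs sites to re-dose after a serious allergic reaction. It does neither: the sections can be reconciled, and nothing in 4.3.4 cancels 4.2. Nor does the 48-hour interval force a decision after a grade 3 or 4 related reaction, since 4.3.2 has already stopped dosing.

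What does not stand is that this closes the gap. The reconciling reading is nowhere stated, and 4.3.4 names two of the examples that 4.2 gives of serious reactions. An SAE report is notification, not the continuation review, and reactions below the SAE threshold need no such report.

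**Conclusion.** The point holds as an unstated limit on 4.3.4, not as a missing stopping rule. The place to which Table 4 sends sites gives a default, premedicate and continue, that differs from the 4.2 default for overlapping reactions, and it does not say which governs. The residual risk is re-dosing without the 4.2 evaluation and Sponsor discussion, either after recovery from a grade 3 or 4 reaction or directly after a lower-grade one.

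Its size cannot be stated as a probability. The protocol gives no rate of serious allergic reactions and none of re-dosing without review. The two-of-three overlap and the absence of any mention of 4.2 measure the drafting gap, not harm to patients. The conclusion assumes that sites manage a reaction mainly from the tables and the section they cite; a site that keeps 4.2 in view is not misled. The change is worth making because it concerns patient safety and costs little.

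**What to change.** Open 4.3.4 with: *For HQP1351 allergy or serious allergic reactions as defined in 4.2, withhold HQP1351 and apply 4.2 before any further dose; the prophylaxis below applies only to reactions that do not meet 4.2 or to subjects continued under the 4.2 exception.* Change the Table 4 cell for administration related reactions to: *Please refer to 4.2 and 4.3.4.*

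Withholding the drug pending the 4.2 decision is a small added step that 4.2 does not contain, and the amendment should say so. Its downside is possibly a missed dose, one of 28 / 2 = 14 scheduled doses in a cycle. Otherwise the cost is one sentence and one table cell in the next amendment, with a notice to sites; no visits, procedures or subjects are added.

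The 4.2 threshold and its exception stay as they are. Allergy to HQP1351 is ungraded in 4.2, so a mild drug-attributed urticaria could be read as meeting it. Whether to attach a grade is for the sponsor's medical team.
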